## Introduction

Endovascular aneurysm repair (EVAR) of the abdominal aorta has become the primary treatment of patients with an abdominal aortic aneurysm (AAA).^1^ Both the Society for Vascular Surgery (SVS) International Guidelines and the instructions for use (IFU) of endograft manufacturers recommend yearly imaging surveillance for all patients after EVAR.^2^ However, if the patient is classified as ‘low risk’ for complications based on initial post-operative imaging, the 2019 European Society for Vascular Surgery (ESVS) guidelines recommend delaying imaging until 5 years after repair.^3^ This movement towards reducing the imaging frequency will benefit patients, medical centres and healthcare costs.

Imaging surveillance by CT angiography (CTA) may increase the attributable lifetime cancer risk of patients, as well as putting them at risk of developing nephropathy due to contrast exposure. If yearly CTA is replaced by duplex ultrasonography (DUS) patients still experience the burden of additional hospital visits. Moreover, compliance with yearly imaging is suboptimal and non-adherence to yearly imaging does not appear to be associated with poorer outcomes.^4 5^

It has been questioned whether yearly imaging is necessary for all EVAR patients, and if a specific group of patients can be identified for which surveillance intervals can safely be extended, as is suggested by the new guideline.^3^ For these reasons, in the Netherlands the Observing a Decade of Yearly Standardised Surveillance in EVAR patients with Ultrasound or CT Scan (ODYSSEUS) study has been designed. In this study of approximately 2000 patients with 6–11 years of follow-up, we aim to determine when, and in which patients, it is safe to deviate from the current annual surveillance protocols.

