## Study objectives

The objective of this study is to evaluate whether imaging surveillance frequency might have been safely reduced in a selected group of EVAR patients, for example, in patients with an asymptomatic or symptomatic infrarenal AAA who underwent EVAR and who had no abnormalities on the 3-month postoperative CTA. The clinical course of a large cohort of patients will be evaluated with follow-up ranging between 6 and 11 years. Baseline patient characteristics, aortic anatomy and details of the operation will be derived from the patient’s medical record. The first milestone during follow-up is the first postoperative CTA. This scan either shows complications such as endoleaks, malposition or migration of the graft, or the absence thereof. All follow-up visits, imaging studies, as well as all interventions after EVAR and outcomes will be registered. Our hypothesis is that patients with less follow-up will have better outcomes regarding the number of interventions and aneurysm-related mortality compared to patients with annual follow-up. Regarding the intervention rates, it is expected that adherence to imaging surveillance may detect more abnormalities triggering re-interventions which in itself may cause additional complications and perhaps even a decrease in survival rates. We hypothesise that the need for routine imaging for patients with no abnormalities at their initial CTA can be decreased.

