### Study population

Patients eligible for this retrospective study are all adults who underwent elective EVAR for asymptomatic or symptomatic infrarenal AAA between January 2007 and January 2012. Table 1 gives a more detailed overview of the inclusion and exclusion criteria.

**Table 1 T1:** Retrospective cohort

Inclusion criteria	Exclusion criteria
Age ≥18 years	Connective tissue disease
Patient with an (a)symptomatic infrarenal abdominal aortic aneurysm EVAR between January 2007 and January 2012	Patients who objected to their retrospective data being used
Patients with an initial postoperative CTA within 90 days after EVAR	

CTA, computed tomography angiography; EVAR, endovascular aneurysm repair.

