### Study procedures

The primary outcomes of this study are interventions and aneurysm-related mortality for patients who had a normal initial postoperative CTA and who do adhere to our definition of yearly imaging surveillance over a 6-year to 11-year follow-up period, compared to those who do not adhere to our definition.

Interventions are EVAR-related interventions defined by the SVS reporting standards as postoperative adjunctive manoeuvres.^16 17^ Interventions for wound complications at the access site are not included, since these are detectable without the use of imaging.

Date of death during follow-up, if applicable, will be obtained from patient medical records and verified by the Dutch municipal personal records database (GBA).

Details of all surveillance imaging are obtained from patient medical records and radiology reports. The time between imaging appointments is calculated to determine whether patients adhere to this studies definition of with yearly imaging surveillance, that is, within every 16 months.

Date, type, indication and outcome of all postoperative imaging during follow-up are obtained from patient medical records, specifically imaging order forms and radiology reports. A normal initial postoperative CT scan is defined as a CT scan which shows no endoleaks, endograft migration (>10 mm), kinking or obstruction. All imaging outcomes are based on the report compiled by radiologists. These reports will not be re-evaluated by an independent radiologist, since we want to base our outcomes on real life data.

Secondary outcomes are all-cause mortality, type I, type II, type III and type IV endoleak, graft or outflow (iliac) occlusion, aneurysm rupture and endograft infection. This is also obtained from patient medical records, specifically radiology reports and Dutch municipal personal records database (GBA).

Date of aneurysm rupture is obtained from patient medical records, specifically operative reports, radiology reports and progress notes.

Costs of all EVAR-related imaging and outpatient clinic visits will be calculated per patient. Cost is defined as volume times price. Prices from the ‘Cost manual of the Dutch Health Care Institute’’ will be used. Costs for the patients will also be included. The quality-adjusted life years, a generic measure of disease burden including both the quality and quantity of life, cannot be calculated with this retrospective design.

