### Statistical methods

Differences in baseline characteristics between patients undergoing or not undergoing yearly standardised imaging surveillance by either CTA or DUS, will be analysed using the χ^2^ or Fisher's exact test for categorical variables and the student's t-test or Mann-Whitney test for continuous variables, if appropriate.

The primary endpoints, that is, survival and freedom from intervention will be estimated by Kaplan-Meier survival analysis and differences between groups will be assessed with the log-rank test.

Secondary endpoints such as freedom from aneurysm rupture between patients with and without yearly standardised imaging surveillance will be estimated by Kaplan-Meier survival analysis, and differences between these groups will be calculated with the log-rank test.

Multivariable cox regression analysis will be used to determine survival and the freedom of intervention corrected for age, gender, AAA diameter, ASA classification, neck length, neck angulation and type of endograft. The association between postoperative intervention and the following covariates will be investigated with the multivariate Cox-regression analysis:

Age.Gender.AAA diameter.ASA classification.Neck length (>15 mm).Neck angulation (>60°).Type of endograft.Initial postoperative CTA.

All statistical analyses will be done with SPSS software (IBM, V.25). The level for statistical significance is set at a p value <0.05. The proportion of missing data will be displayed. The missing values will be imputed by multiple imputation techniques if this does not exceed 10%–15% and conduct a sensitivity analysis to investigate the effect of the missing data on the results of the analysis. If missing data on outcome variables exceeds 15%, we plan to perform subgroup analysis.

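### Neither Cox covariate list includes symptomatic presentation, although the cohort mixes asymptomatic and symptomatic aneurysms and the study asks which patients can have less imaging

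*Protocol article*

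**What the plan says.** Study population admits "all adults who underwent elective EVAR for asymptomatic or symptomatic infrarenal AAA between January 2007 and January 2012", and Table 1 gives the inclusion criterion as "Patient with an (a)symptomatic infrarenal abdominal aortic aneurysm". The Abstract, Study objectives and Discussion describe the cohort in the same mixed terms. The Introduction states the aim as finding out when, and for whom, annual surveillance can safely be relaxed.

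The main comparison is between "patients who had a normal initial postoperative CTA and who do adhere to our definition of yearly imaging surveillance" and patients with a normal first scan who do not adhere. Membership depends on whether imaging took place at least every 16 months, so it is not randomised.

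Statistical methods plans Kaplan-Meier curves with log-rank tests, then a multivariable Cox model for survival and freedom from intervention, "corrected for age, gender, AAA diameter, ASA classification, neck length, neck angulation and type of endograft". A second Cox list, for associations with postoperative intervention, repeats those seven items and ends "Type of endograft.Initial postoperative CTA". Both lists name their variables one by one. Neither is introduced as a set of examples, and no rule is given for adding a variable. The section also plans to compare baseline characteristics between the surveillance groups, but does not tie the result to the choice of covariates.

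On data collection, Study objectives says: "Baseline patient characteristics, aortic anatomy and details of the operation will be derived from the patient’s medical record". Symptom status is not named there as an item.

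**The concern.** The eligibility criteria are written around presentation, yet presentation is absent from both models. Two things follow.

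First, the Cox model is the only planned adjustment of a non-randomised comparison. A baseline factor that is related both to outcome and to keeping yearly imaging would leave some confounding in the adjusted hazard ratio. Presentation is a plausible candidate.

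Second, the predictor model is the part of the plan closest to the question of which patients can be imaged less often. Without a term for presentation it cannot say whether symptomatic patients differ in later intervention, although Study objectives includes them in its example of a target group. This second gap needs no assumption about confounding and exists even if presentation is perfectly balanced between the surveillance groups.

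**Working it through.** **Reproducing the plan's figures.** Sample size and power takes 75% and 82% free of intervention at 7 years, 90% power and a 0.05 significance level. With a two-sided test and unpooled variance:

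n = (1.960 + 1.282)² × (0.75×0.25 + 0.82×0.18) / 0.07² = 718.6, so 719 per group and 1438 in total, as stated. (The pooled formula gives 722.)

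For aneurysm-related mortality, a standard proportion of 0.95, a 3% margin, one-sided 0.05 and 80% power give 653 per group, also as stated.

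**Events available to the models.**
- Interventions by 7 years: 719×0.25 + 719×0.18 = 179.75 + 129.42 = about 309.
- Aneurysm-related deaths: 1438×0.05 = about 72.

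**Cost of one more term**, counting each named covariate as one term and going from seven to eight:
- Interventions: 309/7 = 44 falls to 309/8 = 39 per covariate.
- Aneurysm-related deaths: 71.9/7 = 10.3 falls to 71.9/8 = 9.0. The Cox sentence names survival and freedom from intervention, so this applies only if a similar model is fitted to aneurysm-related death.
- ASA class and endograft type may each need several terms, which lowers all these ratios.

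**Possible confounding.** Let H be the hazard ratio of symptomatic against asymptomatic patients, and pA and pB the symptomatic shares with and without yearly imaging. Leaving presentation out multiplies the hazard ratio (no yearly imaging v yearly imaging) by

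[1 + pB(H − 1)] / [1 + pA(H − 1)].

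The documents give none of H, pA or pB, so every input below is an assumption.

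| H | pA | pB | Factor |
|---|---|---|---|
| any | 10% | 10% | 1.00 |
| 1.2 | 10% | 20% | 1.02 |
| 1.2 | 20% | 10% | 0.98 |
| 1.5 | 10% | 15% | 1.02 |
| 1.5 | 15% | 10% | 0.98 |
| 2.0 | 10% | 20% | 1.20/1.10 = 1.09 |
| 2.0 | 20% | 10% | 1.10/1.20 = 0.92 |

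**Against the planned effect.** The planned hazard ratio is ln 0.82 / ln 0.75 = 0.69. At the extremes it would be seen as 0.69×0.92 = 0.63 or 0.69×1.09 = 0.75. The standard error of the log hazard ratio is roughly 2/√309 = 0.11. The largest shift, ln 1.09 = 0.087, is therefore about three-quarters of a standard error. A 2% shift is about one-fifth.

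**The case against.** The strongest reply is that seven sensible covariates are stated without contradiction, and that an eighth is a matter of preference. Several parts of that reply stand.

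- A reader might infer that symptomatic patients are known to be at different risk. No section says so; a risk difference is plausible but undocumented.
- A reader might infer that the adjusted comparison is biased. That also needs presentation to be unbalanced between patients who do and do not keep to the 16-month rule. No section links the two, and the survey described under Background gives forgotten appointments and force majeure as the main reasons for missed visits. Restriction to elective repair and a normal first scan, with adjustment for diameter and ASA class, may already absorb part of any difference.
- A reader might infer that presentation is on file for every patient. A criterion that admits both kinds does not require telling them apart, and the article warns that only documented data can be collected.
- A reader might want baseline renal function added too, because the Introduction describes CTA as "putting them at risk of developing nephropathy due to contrast exposure". That passage concerns a harm of one imaging method. Adherence counts CTA or duplex ultrasound, so a patient who avoids contrast can still be in the yearly group. No link to group membership is documented, and renal function is not named as an extracted item. The point does not extend to it.

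What the reply does not answer is the gap in the predictor model. It can be said that the article treats the two presentations as one population and defines low risk by the first scan alone. But a study that asks in which patients imaging can be reduced, and mixes presentations by design, gains from a term that shows whether they differ.

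**Conclusion.** The point holds as a modest improvement. Both Cox lists are fixed by name and omit a characteristic on which the cohort is described throughout. The adjusted hazard ratios may keep some confounding if presentation is both prognostic and unevenly spread. The factor is 0.92 to 1.09 for an assumed hazard ratio of 1.2 to 2.0 and a share difference of 0 to 10 points, and 1.00 with equal shares. Nothing in that range reverses the expected direction. The omission also leaves the predictor model silent on whether symptomatic patients differ in later intervention, and that part rests on no assumed figure.

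The documents do not support reading this as a demonstrated bias or as a fault in the main test. The log-rank comparisons are unadjusted whatever the lists contain, and the sample size is unchanged.

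**What to change.** In Statistical methods, add symptomatic presentation (yes/no) to both Cox covariate lists, taken from the medical records with the other baseline characteristics. If it is to stay out, give the reason.

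The change is to the wording of two lists and costs one degree of freedom in each model. With about 309 expected interventions the loss of precision is negligible. If a similar model is fitted to the roughly 72 aneurysm-related deaths, the cost is slightly larger, because events per covariate fall just below 10. Data collection grows only if presentation is not already being extracted.

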**Trial registration number:**

The Netherlands Trial Registry, NL6953 (old: NTR28773).

Strengths and limitations of this studyThe main strength of this study is that it can accumulate data from large number of patients with long-term follow-up up to 11 years and that it captures all surveillance visits, long-term outcomes and mortality post-endovascular aneurysm repair.The sample size will be large enough to enable survival and regression analyses in sub-groups of patients.The main limitation of the study is due to the nature of retrospective data, it allows only the collection of data that was documented in the patient medical records.

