**Figure 1 F1:**
[figure not shown]
Patient subgroups. AAA, abdominal aortic aneurysm; CTA, CT angiography; EVAR, endovascular aneurysm repair.

The standard of care is defined by the current guidelines and IFU. The usual follow-up schedule in the IFU is: CTA and abdominal X-ray at 30 days, 6 and 12 months and yearly thereafter. The 2019 ESVS guidelines recommend a CTA 30 days after EVAR. If there is adequate seal and no endoleak, patients are classified as low risk and CTA follow-up may take place 5 years later. If there is an inadequate seal and endoleak type I/III patients could be either evaluated for re-intervention or if sac shrinkage occurs yearly DUS is recommended. In the 2018 SVS guideline, CTA at 1 and 12 months is recommended and if neither endoleak nor sac enlargement is documented, DUS is suggested for annual postoperative surveillance. In our study design, the definition of compliance is undergoing imaging surveillance every 16 months since patients in most centres will be rescheduled if they missed their annual follow-up visit. Device-specific complications after EVAR will also be examined.

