## Discussion

The goal of this study is to evaluate whether a reduction in follow-up visits and imaging and thus costs, in patients operated on for an asymptomatic or symptomatic AAA with EVAR is safe. We hypothesise that there will be less interventions and no difference in aneurysm-related mortality in patients with less intensive follow-up. With the results of this study, we aim to provide scientific evidence helping vascular surgeons decide whether less vigilant follow-up after EVAR may be considered for patients classified in the low risk group.

The strengths of the ODYSSEUS study are that it can accumulate the data of a large number of consecutive EVAR patients with a theoretical follow-up of 6 to 11 years, and that it captures all surveillance visits, long-term outcomes and mortality post-EVAR. Moreover, 17 medical centres throughout the Netherlands are participating in this study, including university and general hospitals, thereby reducing selection bias.

An e-survey has been sent to all vascular surgeons participating in the ODYSSEUS study. This shows that yearly imaging surveillance is upheld by most vascular surgeons in the Netherlands. In addition, most physicians agree that yearly imaging frequency can be safely reduced in a specific group of EVAR patients. As support for this reduction in frequency is evident in the Netherlands, the next step will be to study the groups for which it will be safe to deviate from the widely accepted surveillance protocols.

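### The protocol aims to find in which patients less imaging is safe, but it describes only an average comparison in normal-CTA patients and a prognostic model without surveillance; neither shows how the surveillance contrast varies between patients.

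*Protocol article*

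**What the plan says.** **Aim.** The Introduction states: "we aim to determine when, and in which patients, it is safe to deviate from the current annual surveillance protocols". Study objectives speaks of whether one could "evaluate whether imaging surveillance frequency might have been safely reduced in a selected group of EVAR patients", with a normal early CTA given as an example of such a group. The Discussion says "the next step will be to study the groups for which it will be safe to deviate from the widely accepted surveillance protocols". The strengths and limitations list after the abstract claims: "The sample size will be large enough to enable survival and regression analyses in sub-groups of patients".

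**Design.** General study design forms three groups: A (normal first CTA, yearly imaging), B (normal first CTA, no yearly imaging) and C (abnormal first CTA). Study procedures makes A versus B the primary comparison. The exposure is set in the text after Figure 1: "the definition of compliance is undergoing imaging surveillance every 16 months".

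**Analysis.** Statistical methods plans Kaplan-Meier and log-rank comparisons and then two Cox analyses.
- The first: "Multivariable cox regression analysis will be used to determine survival and the freedom of intervention corrected for age, gender, AAA diameter", followed by ASA class, neck length, neck angulation and endograft type. The exposure is not named; surveillance group is the natural reading.
- The second: "The association between postoperative intervention and the following covariates will be investigated with the multivariate Cox-regression analysis". The list reads "Age.Gender.AAA diameter.ASA classification.Neck length (>15 mm).Neck angulation (>60°).Type of endograft.Initial postoperative CTA".

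**The concern.** Asking in which patients less imaging is safe is a question about effect modification: does the difference between B and A depend on the kind of patient? To answer it, an analysis must contain surveillance and let its effect vary with a patient factor.

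The second Cox model does neither. It estimates which patients receive an intervention. A factor can predict intervention strongly where imaging makes no difference, or weakly where imaging matters. Study objectives also expects imaging to find abnormalities that trigger re-intervention, so intervention is partly a product of surveillance. A low predicted intervention rate is then not evidence that imaging can be spared.

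At stake is a headline aim of the study. The average A-B comparison can be sound and still leave that aim without an analysis that answers it beyond the normal-CTA group as a whole.

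**Working it through.** **1. What each planned analysis estimates**

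| Analysis | Contains surveillance? | Effect allowed to vary by patient factor? | Outcome |
|---|---|---|---|
| Kaplan-Meier and log-rank | Yes, as the grouping | No, beyond the normal-CTA restriction in Study procedures | Survival, intervention, rupture |
| First Cox model | Presumably (exposure not named) | No | Survival, intervention |
| Second Cox model | No (eight covariates listed) | No | Intervention |

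No row gives an A-B contrast that differs between patients. Because initial CTA is a covariate in the second model, that model must also include patients with an abnormal scan. It is therefore not confined to the normal-CTA patients about whom the surveillance question is asked.

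**2. The protocol's sample size reproduces**

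Inputs from Sample size and power: 75% and 82% intervention-free at 7 years, 90% power, 0.05 significance level (taken as two-sided).

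n per group = (1.960 + 1.282)² × (0.75×0.25 + 0.82×0.18) / 0.07² = 718.6, so 719 as stated.

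The non-inferiority figure of 653 per group also reproduces, with 0.95 in both groups, a 3% margin, one-sided 0.05 and 80% power. Both calculations size the average A-B contrast; neither concerns variation between patients.

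**3. What an interaction analysis could deliver for intervention**

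Expected first interventions by 7 years in A and B: 719×0.25 + 719×0.18 = 309.

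For a two-level factor with prevalence p, and events split about equally between A and B, the standard error of the interaction on the log hazard ratio is

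SE = √[4/(E·p) + 4/(E·(1−p))]

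The protocol gives no factor prevalences, so these are assumed.

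| p | SE (E = 309) | 95% limits: estimate × or ÷ |
|---|---|---|
| 0.50 | 0.23 | 1.56 |
| 0.30 | 0.25 | 1.63 |
| 0.15 | 0.32 | 1.87 |

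Power is low. With variance v = (0.1875 + 0.1476)/719, the difference between two stratum-specific risk differences has SE √[v/p + v/(1−p)]. For an interaction as large as the whole 7-point main effect, power is about 37% at 50:50, 32% at 30:70 and 16% at 10:90.

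**4. The same for aneurysm-related death**

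Taking 5% by 7 years, the value that reproduces 653: 1438×0.05 = 72 deaths.

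| p | SE (E = 72) | 95% limits: estimate × or ÷ |
|---|---|---|
| 0.50 | 0.47 | 2.5 |
| 0.30 | 0.51 | 2.7 |
| 0.15 | 0.66 | 3.6 |

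The sample size section also mentions 0.97. At 3% there would be 1438×0.03 = 43 deaths, and the SE would be 0.61 (p = 0.50) to 0.85 (p = 0.15).

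**The case against.** The strongest reply is that the patients are selected by design. Study objectives offers normal first CTA as the selected group, the A/B/C split rests on that scan, and the conclusion of the Discussion speaks of confirming a guideline that defines low risk by early imaging. On that reading A versus B is the answer, and the second Cox model is a side analysis of prognosis. Much of this stands: the A-B comparison does answer the question for that one group. It does not dispose of the point. The Introduction and Discussion speak of finding patients and groups, normal CTA is only an example in Study objectives, and nothing described distinguishes patients within the normal-CTA group.

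Three stronger readings are tempting, and the document does not support them.
- *A reader might infer that the second model will be used to pick patients for reduced imaging.* No section says so; it is presented only as an association analysis.
- *A reader might infer that surveillance is absent from all modelling.* The first Cox model presumably contains it.
- *A reader might infer that safety is not examined.* Aneurysm-related mortality is a primary endpoint by surveillance group with a 3% margin, and freedom from rupture is compared between surveillance groups.

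It may also be said that subgroup details belong in a fuller plan. That is fair for the choice of subgroups. But the covariate list is written out here, and the article claims sub-group capacity without linking it to the surveillance contrast.

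Finally, interaction tests would be imprecise and numerous: four factors on two outcomes make eight. This stands, and it is why the added analysis should be exploratory.

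**Conclusion.** The point holds as a mismatch between a stated aim and the analyses described. The average A-B comparison is unaffected and serves the narrower question. The listed covariate model is prognostic and cannot show in whom less imaging is safe, and no described analysis examines how the A-B contrast varies.

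The study could give usable though imprecise estimates for intervention, with limits within a factor of about 1.6 to 1.9. For aneurysm-related death the factor is about 2.5 to 3.6 at 5% mortality, too wide for more than description. These figures assume the planned 719 per group, the protocol's 7-year rates, events split roughly evenly between A and B, and factor prevalences of 15% to 50%. Unequal adherence groups would widen them.

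This should be repaired, but it does not threaten the primary comparison.

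**What to change.** In Statistical methods:

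1. Within the normal-CTA patients (A and B), fit a Cox model for intervention containing surveillance, coded as in the main comparison, and a surveillance-by-factor interaction for a short fixed list already collected, for example AAA diameter, neck length, neck angulation and endograft type.
2. Report the A-B contrast with confidence limits in each stratum, labelled exploratory, with the limited power stated.
3. For aneurysm-related death or rupture, show the stratum results descriptively only.
4. State that the listed eight-covariate model is prognostic and will not be used to select patients for reduced imaging.

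In the strengths and limitations list, qualify the sub-group claim: the sample was sized for the average A-B contrast, not for differences between subgroups.

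The least that would remove the mismatch is to narrow the aim in the Introduction and Discussion to the average effect in patients with a normal first CTA.

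The cost is a few extra models on data already being collected. The downside is wide estimates, several low-power comparisons, and a more cautious conclusion about subgroups.

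### The secondary risk-factor Cox model counts early repairs of a finding on the first CTA as events, so its hazard ratio for an abnormal CTA can exceed 1 with no difference in later risk

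*Protocol article*

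**What the plan says.** Statistical methods describes two Cox analyses. The first adjusts survival and freedom from intervention for a set of baseline factors and does not list the first CTA. The second is a risk-factor analysis: "The association between postoperative intervention and the following covariates will be investigated with the multivariate Cox-regression analysis". Its covariate list ends with "Type of endograft.Initial postoperative CTA".

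Study procedures defines the event: "Interventions are EVAR-related interventions defined by the SVS reporting standards as postoperative adjunctive manoeuvres". One exclusion follows: "Interventions for wound complications at the access site are not included, since these are detectable without the use of imaging". The same section defines the covariate: "A normal initial postoperative CT scan is defined as a CT scan which shows no endoleaks, endograft migration (>10 mm), kinking or obstruction".

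Table 1 allows the initial CTA up to 90 days after EVAR. No landmark, and no start of risk after that scan, is stated for the Cox model. The secondary endpoints list the date and type of each intervention. They list an indication for imaging but not for interventions.

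**The concern.** An abnormal first CTA can itself be the reason for an intervention. The article recognises this mechanism in general terms in Study objectives, where it expects that "adherence to imaging surveillance may detect more abnormalities triggering re-interventions". In describing the 2019 European guideline under General study design it also says: "If there is an inadequate seal and endoleak type I/III patients could be either evaluated for re-intervention". Because the event includes every EVAR-related procedure apart from access-site wound care, treatment of the finding is counted as the outcome with which the finding is associated.

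The study wants to know for whom imaging can be reduced: "We hypothesise that the need for routine imaging for patients with no abnormalities at their initial CTA can be decreased". Used as a selector, the first CTA has to separate patients by their risk after the scan has been read and acted on. A repair in the first months of a leak seen on that scan says little about whether later yearly imaging is needed. A hazard ratio that combines the two could be taken as evidence of long-term risk separation when part of it, possibly most, is early treatment.

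**Working it through.** **The plan's own figures.** The article gives no figure for this model, so the sample-size inputs are used. For 75% v 82% intervention-free at 7 years, 90% power and two-sided 0.05, with unpooled variance:

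n = (1.960 + 1.282)² × (0.75×0.25 + 0.82×0.18) / 0.07² = 718.6, so 719 per group, as stated.

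The total is 1438. Dividing by 0.8 gives 1797.5, stated as 1798. The calculation reproduces and is not affected by this point.

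**Inputs from the article (Sample size and power; General study design).**
- 1798 patients, about 20% with an abnormal first CTA: 0.20 × 1798 ≈ 360.
- Intervention-free at 7 years: 75% or 82%. As constant hazards, −ln(0.75)/7 = 0.0411 and −ln(0.82)/7 = 0.0284 per year.
- Theoretical follow-up of 6–11 years.

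**Assumptions not in the article.**
- A share q of abnormal-CTA patients has a corrective procedure between about 1 and 6 months after EVAR. The values used are 0%, 5%, 10%, 20% and 30%, which is 0, 18, 36, 72 and 108 patients.
- Death or loss runs at 7% per year, and administrative censoring is uniform over 6–11 years.
- The later intervention hazard is the same in both CTA groups, so the true later hazard ratio is 1.

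**Simulated Cox model, all interventions counted from EVAR.**

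| q | HR (75%) | p<0.05 (75%) | HR (82%) | p<0.05 (82%) |
|---|---|---|---|---|
| 0% | 1.00 | 6% | 1.01 | 5% |
| 5% | 1.24 | 50% | 1.34 | 59% |
| 10% | 1.47 | 89% | 1.66 | 98% |
| 20% | 2.06 | 100% | 2.44 | 100% |
| 30% | 2.72 | 100% | 3.33 | 100% |

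There were 200 replicates per row at 75% and 100 at 82%. A separate simulation used the midpoint hazard (0.0346 per year), 6% deaths per year and follow-up of 6.9–11.9 years. It gave 1.22, 1.50, 2.10 and 2.83 for q of 5%, 10%, 20% and 30%.

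**Hand check.** Let d be the expected number of first interventions per patient without early correction. With hazard λ, a = λ + 0.07 and censoring uniform over 6–11 years:

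d = (λ/a) × [1 − (e^(−6a) − e^(−11a))/(5a)]

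This is 0.224 at 75% and 0.162 at 82%. Corrected patients add q events and almost no person-time, so the rate ratio is about 1 + q/[(1−q)d].
- At 75%, q = 10%: 1 + 0.1111/0.224 = 1.50 (simulated HR 1.47).
- At 82%, q = 10%: 1 + 0.1111/0.162 = 1.69 (simulated HR 1.66).
- At 75%, q = 5%: 1 + 0.0526/0.224 = 1.23 (simulated HR 1.24).

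The formula runs somewhat above the Cox estimate at large q, because the excess is confined to the first months and hazards are then not proportional. The mechanism and size agree.

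**Landmark.** Starting at 6 months and counting only later interventions gave 0.99–1.02 across these settings (not run at 82%). This follows from how the data were generated: all corrective procedures fall before 6 months and later hazards are equal. It shows that the landmark targets the intended quantity. It does not show how well it works if correction comes later.

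**The case against.** The strongest reply is that the model claims only an association. For the outcome as defined, a corrective procedure is a genuine event, and total intervention risk by first-CTA result is a legitimate description. That stands, and is why the all-intervention model should be kept for that purpose. It does not answer the selection question.

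A second reply is that time origin and early-event rules are often left to an analysis plan, and none is shown. An unseen plan may indeed add a landmark. But the article does fix the event, its single exclusion and the covariate, and following these as written counts the corrective procedures. This is inferred from the definition; the article does not say it outright.

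Third, the sentence on type I/III endoleak describes a 2019 guideline, while the cohort had EVAR from 2007 to 2012 with follow-up to December 2018. A reader might infer that it governed these patients' care. It did not, and even there re-intervention is one of two routes. It only illustrates that such findings can lead to intervention; how often they did here is not stated.

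Fourth, a reader might infer that the main result is biased. It is not: Study procedures restricts the primary comparison to patients with a normal first CTA, with v without yearly imaging. The hypothesis about reducing imaging in those patients is addressed by that comparison, not by this hazard ratio.

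**Conclusion.** The point holds for the secondary risk-factor model. As specified, its hazard ratio for an abnormal first CTA combines early correction with later risk and can exceed 1 when later risk is equal.

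The size depends on an early-correction share that the article does not give. The apparent hazard ratio is about 1.2–1.3 at 5%, 1.5–1.7 at 10%, 2.1–2.4 at 20% and 2.7–3.3 at 30%. Even at 5%, about 18 patients, p<0.05 arises in 50–59% of simulated studies. These figures assume constant later hazards, corrections within 6 months and 7% per year death or loss.

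A reader might infer that an abnormal CTA will necessarily look strongly prognostic, or that it has no real later association. The article supports neither. The distortion is modest at 5% and reaches 2 or more only from about 20%. A true later association may exist; the planned model cannot separate it from early treatment. This is a worthwhile and cheap improvement to one secondary analysis and does not undermine the primary comparison.

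**What to change.** For any inference about the first CTA as a selector for less imaging:

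- Fit the risk-factor model from a prespecified landmark after the 90-day CTA window, for example 6 months after EVAR, with a second landmark such as 12 months as a sensitivity analysis.
- Code the first CTA as normal, abnormal not treated by the landmark, or abnormal treated by the landmark.
- Take the first intervention after the landmark as the event.
- Report interventions before the landmark descriptively.
- Present the all-intervention model alongside, labelled as total intervention burden only.

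The choice of 6 months is an example and does not come from the article. The change needs only CTA results and intervention dates, both already collected. Separating interventions by indication instead would need a data item that is not listed for interventions.

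The cost is the loss of early events and of patients who die or are censored before the landmark. Under the constant hazards above, first interventions unrelated to early correction would be lost in 1 − e^(−0.0411×0.5) = 2.0% of patients (about 37 of 1798) at 75%, or 1 − e^(−0.0284×0.5) = 1.4% (about 25) at 82%. Death or loss at 7% per year would remove 1 − e^(−0.07×0.5) = 3.4% (about 62). Corrections made after the landmark would still count as events, which is why a later second landmark is useful.
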